1.3.4.3 Phase II Clinical Trials for Efficacy and Safety Evaluation

The phase II exploratory clinical trial adopted a parallel control design with groups receiving injectable L-oxiracetam (3g/ day, 4g/ day), a positive control group receiving oxiracetam, and a placebo group, each conducted in a 1:1:1:1 ratio for efficacy and safety exploration, totaling 200 participating subjects. Preliminary statistical analysis of the phase II clinical study using the Per Protocol Set (PPS) indicated that three months post-treatment, the changes in the Loewenstein Occupational Therapy Cognitive Assessment (LOTCA) scale total scores from baseline were as follows: high dose group (4g/ day) 26.0 ± 11.8, low dose group (3g/ day) 22.2 ± 10.3, positive control group 22.8 ± 10.0, and placebo group 20.0 ± 11.4. The high dose group (4g/ day) showed statistically significant improvements compared to the placebo group (P < 0.05). The low dose group (3g/ day) did not show a statistically significant difference compared to the placebo group (P > 0.05), but there was a trend of improvement. Phase II safety results indicated that no SAEs related to the test drugs occurred, demonstrating good overall tolerability and safety.

The Phase III clinical trial is planned to be conducted with participants allocated to the high-dose treatment group (4g/ day), a positive control group, and a placebo group in a 2:2:1 ratio.

**1.4 Potential Risks and Benefits**

Since L-oxiracetam has not been marketed domestically or internationally, its clinical risks and benefits are assessed with reference to those of oxiracetam.

1.4.1 Known Potential Risks

Oxiracetam generally has few adverse reactions. However, it can cause anxiety, skin itching, rash, nausea, and stomach pain, which usually resolve after discontinuation of the drug. A reduction in dosage may be necessary for a small number of patients who experience psychiatric excitement or sleep abnormalities. Caution is advised in patients with allergies to this drug or with renal impairment; a reduced dosage should be used if the drug is necessary.

1.4.1.1 International Research Results

Son et al. conducted a human tolerability study confirming that the administration of oxiracetam at doses ranging from 400 to 2000 mg per day did not result in any adverse reactions.^16^ There were no changes in heart rate, blood pressure, respiration, electrocardiogram (ECG), electroencephalogram (EEG), liver, or kidney functions, indicating that oxiracetam is a drug with extremely low toxicity.

Rozzini and colleagues randomly divided 96 patients with cognitive impairments into two groups for a 26-week treatment with either oxiracetam (1600 mg) or a placebo.^17^ The group treated with oxiracetam demonstrated good compliance, and the study confirmed that oxiracetam is well-tolerated at this dosage.

In a one-year study conducted by Villardita et al., involving 60 patients with mild to moderate dementia treated with oxiracetam, no serious adverse reactions were observed.^18^ They concluded that a daily dose of 1600 mg of oxiracetam is safe.

1.4.1.2 Domestic Research Results

Yu and colleagues conducted a human tolerability study on oxiracetam using a starting dose of 200 mg, which is one-tenth of the most common adult dose used internationally (2000 mg/ day), with increments up to the standard international dose of 2000 mg.^19^ The trial included six dosage groups: 400, 800, 1200, and 1600 mg, in addition to the starting and maximum doses. The tolerability trial was carried out in an ascending dose order, with each participant receiving only one dose level. Measurements taken before and after medication included vital signs, neurological function, adverse reactions, and laboratory tests. The results were analyzed using a t-test to compare pre- and post-medication changes. Among the 22 participants who received varying doses, particularly a single oral dose of 2000 mg of oxiracetam, no adverse reactions were observed, and all subjects tolerated the drug well. Besides a significant decrease in triglyceride (TG) levels at doses of 800, 1200, 1600, and 2000 mg (P < 0.05), no significant statistical differences were noted in other measured parameters (P > 0.05).

In a study conducted by He and colleagues on the efficacy of oxiracetam injection in treating Alzheimer's disease, the treatment group received oxiracetam injection added to 5% glucose or saline solution for intravenous infusion.^20^ Each treatment cycle lasted 21 days, followed by a 7-day drug holiday before the next cycle. The control group was administered Cytidine Diphosphate Choline (CDP-Choline) 0.6g added to 5% glucose or saline solution, with the same treatment duration as the therapy group. After three treatment cycles, the effectiveness and safety were evaluated. In the CDP-Choline group, three cases experienced nausea, dizziness, headache, and insomnia, while in the oxiracetam group, two cases reported nausea, vomiting, and stomach discomfort, which improved after symptomatic treatment.

During a clinical observation conducted by Zhao and colleagues involving 327 patients, no adverse reactions were reported.^21^

1.4.2 Known Potential Benefits

Cranial brain injuries are common in neurosurgery and have the highest rates of mortality and disability among all types of trauma. Timely treatment during the acute phase is crucial for reducing both mortality and disability rates. Cognitive impairment and memory decline are the most common sequelae following brain trauma. Early EEG changes characteristic of brain trauma primarily include an increase in δ and θ slow waves, and a reduction in α and β wave power; the proliferation of δ and θ slow waves is often diffuse, which correlates with brain dysfunction after the injury. The power of the slow waves is related to the severity of the injury; more severe brain injuries are associated with higher and more pronounced θ power.

1.4.2.1 International Related Clinical Research

Russello D and colleagues conducted a study with 36 patients who were suffering from post-concussion syndrome, randomly dividing them into two groups.^22^ One group received treatment with oxiracetam. The results indicated that oxiracetam significantly improved the symptoms of patients with post-concussion syndrome. It enhanced the amount of α activity in the EEGs of patients with dementia and reduced δ activity, with the most notable effects observed in the frontal-temporal regions.

1.4.2.2 Domestic Related Clinical Research

Dan and colleagues investigated the effects of oxiracetam on brain function in patients with acute mild brain injuries.^23^ They selected 48 patients who were admitted within 24 hours after injury, all classified with mild brain injuries (Glasgow Coma Scale (GCS) scores between 12 and 15). The study was randomized and double-blind, comparing the effects of oxiracetam with those of piracetam. Changes in brain wave activity were monitored using quantitative EEGs before and after medication, focusing on changes in relative power values and ratios. After medication, changes in EEGs showed that in the oxiracetam group, all patients' indices increased, wave amplitudes rose, and generalized activity decreased. In contrast, only 21 patients in the piracetam group showed these changes, and 3 patients showed insignificant changes; focal activities were not completely eliminated in all cases. The study demonstrated that oxiracetam significantly improves brain function in patients with acute mild brain injuries, showing a stronger effect than piracetam.

Shu and colleagues conducted a randomized double-blind trial involving 120 patients with moderate TBIs, comparing the effects of oxiracetam to the positive control drug piracetam (sold under the brand name Cerebrolysin).^24^ The treatment group received oral oxiracetam capsules at a dose of 2.4g per day, with each treatment cycle lasting 30 days. The efficacy of the treatment was evaluated using several scales: the Mini-Mental State Examination (MMSE), GCS, Glasgow Outcome Scale (GOS), and self-reported symptom scores. The results indicated that among patients treated with oxiracetam, the marked effectiveness rate was 33.3%, the effectiveness rate was 50.0%, and the total effectiveness rate was 83.3%. Oxiracetam demonstrated significant superiority in improving patients' quality of life, cognitive abilities, and memory functions compared to piracetam. These differences were statistically significant (P < 0.05).

Wu and colleagues assessed the clinical efficacy of oxiracetam in the treatment of acute cranial brain injuries.^25^ They enrolled 76 patients who met the study criteria and randomly divided them into two groups: an oxiracetam treatment group with 38 patients and a control group receiving standard treatment, also with 38 patients. The study observed changes in the GCS scores during different periods of the treatment and the GOS scores at the end of the treatment and during the recovery period. The results indicated that the GCS scores of the oxiracetam treatment group were significantly better than those of the control group after 7 days of medication (P < 0.05). GOS scores assessed at the end of the 2-week treatment period and again 4 months later during follow-up also showed that the treatment group had significantly better outcomes than the control group (P < 0.05). Mortality rates were evaluated at the end of the follow-up period, with 5 deaths (10.4%) in the treatment group compared to 12 deaths (25.0%) in the control group, demonstrating a statistically significant difference (P < 0.05). The study concluded that early use of oxiracetam in the treatment of acute cranial brain injuries is effective, has few adverse reactions, significantly reduces mortality rates, and improves prognosis.

**2 Trial Objectives**

- Primary objectives
- To evaluate the efficacy of L-oxiracetam on functional outcome in patients with TBI.
- To evaluate the safety of L-oxiracetam in patients with TBI.
- Secondary objectives
- To analyse changes in function and disease severity of patients with TBI treated with either L-oxiracetam, oxiracetam or placebo.
- Exploratory objectives
- To evaluate influence in subgroup (such as age, gender and so on) in patients with TBI treated with either L-oxiracetam, oxiracetam or placebo.

**3 Trial Design**

**3.1 Summary of Trial Design**

This multicenter study is a randomized, double-blind, parallel, three-arm, phase III clinical trial. The design and implementation of this trial strictly adhere to the Helsinki Declaration and have obtained approval from the ethics committees of each research center. This trial was approved by the China National Medical Products Administration (Approval Number, 2016L03521) and registered on chinadrugtrials.org.cn (identifier, CTR20192539) and ClinicalTrials.gov (identifier, NCT04205565). The rights and safety of the subjects in this trial are prioritized over the benefits to science and society.

The trial is planned to be conducted in 74 centers across 51 hospitals in China (see **Appendix 1**), and subjects will not be enrolled in the study until written informed consent (see **Appendix 2**) is obtained from the subjects and/ or their guardians/ legal representatives. All qualified medical centers undergo rigorous training before the start of the study and adhere to standardized treatment for enrolled patients.

Eligible TBI patients will be randomly assigned to three groups: L-oxiracetam group, oxiracetam group, and placebo group in a ratio of 2:2:1. The efficacy and safety of improving memory and cognitive impairment in TBI patients will be observed over a treatment period of 14 days, with a follow-up period of 90 days.

**3.2 Trial Period**

September 2019- May 2024.

**4 Target Population**

**4.1 Eligibility of Target Population**

Patients are aged 18 to 75 years and have mild to moderate (GCS score of 10 to 15) acute TBI.

And investigators and sponsor should discuss with sharing sufficient information regarding the eligibility of patients before the enrollment.

**4.2 Inclusion and exclusion criteria**

4.2.1 Inclusion criteria

- Age 18-75 years;
- Head injury meeting all of the following conditions: 1) Clear evidence of head trauma in the current diagnosis, including closed head injury or head injury with cerebrospinal fluid leakage and/ or ear or nasal leakage and/ or intracranial air accumulation; 2) Confirmed by magnetic resonance imaging (MRI) or computed tomography (CT) to have intracranial bleeding above the cerebellar tentorium (including cerebral contusion, subarachnoid hemorrhage, extradural hematoma, subdural hematoma, intracerebral hematoma, etc.), with or without transient loss of consciousness; 3) Classified as mild to moderate head injury (GCS: 10-15); 4) Stable condition within 72 hours after head injury, undergoing conservative treatment, not undergoing craniotomy (may have intracranial pressure monitoring without general anesthesia or basal anesthesia);
- MMSE score below normal, with diagnostic cutoff values depending on different educational levels: illiterate (no education) ≤ 19 points, elementary school level ≤ 22 points, junior high school and above level ≤ 26 points;
- Consent from the guardian and/ or patient to participate in this clinical trial and signing of the informed consent form.

4.2.2 Exclusion criteria

- Known or suspected allergy to the experimental drug or its components;
- Use of prohibited drugs or other cognitive-enhancing drugs listed in the protocol after injury;
- History of severe head trauma, cerebrovascular accidents, or structural brain lesions;
- Conditions such as speech/ hearing impairment that prevent completion of cognitive function assessment;
- Occurrence of secondary brain injury after the current head injury;
- Need for craniotomy or external ventricular drainage;
- Concurrent serious injuries to other major organs or serious complications that may affect the subject's life;
- Patients with active epilepsy within the past year;
- Severe liver or kidney disease with abnormal liver or kidney function tests (alanine aminotransferase (ALT), aspartate aminotransferase (AST)) ≥ 3 times the upper limit of normal, serum creatinine (Scr) > upper limit of normal);
- Concurrent severe heart disease, lung disease, blood and hematopoietic system diseases, gastrointestinal diseases, or other severe or progressive systemic diseases;
- History or current diagnosis of malignant tumors (excluding cured stage IB or lower cervical cancer, non-invasive basal cell or squamous cell skin cancer; exclusion of breast cancer with complete remission (CR) > 10 years, malignant melanoma with CR > 10 years, and other malignant tumors with CR > 5 years);
- Presence of neurological or psychiatric disorders that prevent or unwillingness to cooperate;
- Pregnant, lactating women, or those with recent plans for childbirth;
- Investigator deems unsuitable for participation in the clinical trial;
- Participation in another clinical trial and use of experimental drugs in the last 3 months before the trial.

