Pharmacotherapy: Currently, there is a lack of large-scale randomized controlled trials and evidence-based medicine supporting pharmacological treatment for cognitive impairments following TBI. The existing pharmacological treatments are based on experiences from small-scale studies or from research on cognitive impairments caused by other types of brain damage, such as Alzheimer's disease and vascular dementia. The medications used include: (1) Drugs primarily acting on the dopaminergic system: Bromocriptine, Levodopa, Methylphenidate, and Amphetamine; (2) Drugs primarily acting on the catecholaminergic system: Meclofenoxate Hydrochloride, Methylphenidate Hydrochloride and Modafinil; (3) Drugs primarily acting on the cholinergic system: Physostigmine, Tacrine, Donepezil, Rivastigmine, and Galantamine; (4) Other drugs: Citicoline and Lamotrigine.

Hormone Replacement Therapy: (1) Growth Hormone: Growth hormone plays a critical role in the growth and development of the central nervous system, particularly evident in promoting brain growth, myelination, differentiation of glial cells, and cognitive functions; (2) Estrogen: Estrogens can increase the synthesis and transmission of neurotransmitters such as acetylcholine, thereby significantly influencing the normal functioning of learning, memory, and cognitive processes; (3) Thyroid Hormone: Thyroid hormones regulate the expression of genes and proteins related to myelination, neuronal migration, differentiation, and maturation. This includes the expression of proteins such as Neural Growth Protein-43, neurogranins, calmodulin-dependent protein kinase, and extracellular signal-regulated kinases, thereby affecting brain functions including learning and memory.

Cognitive Rehabilitation: Cognitive rehabilitation is a therapeutic approach designed to enhance cognitive function in patients with brain injuries. Current methods of cognitive rehabilitation primarily include occupational therapy, implicit memory rehabilitation, errorless learning, cognitive neuropsychological rehabilitation, computer-assisted and virtual cognitive rehabilitation, remote-controlled cognitive rehabilitation via the internet, and electromagnetic stimulation.

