**6.2 Prohibited Medications and Treatments**

Post-injury cognitive rehabilitation treatments are not allowed. During the medication and follow-up periods, the use of drugs that might affect the efficacy evaluation is prohibited, including:

- Cholinesterase inhibitors such as donepezil, rivastigmine, galantamine, tacrine, and huperzine A.
- γ-lactam brain function enhancers, such as aniracetam, piracetam, oxiracetam, and other commercially available forms.
- Other medications such as nimodipine, vinpocetine, ginkgo biloba extracts, cerebrolysin, amantadine/ robenidine, gangliosides, citicoline, idebenone, amantadine, glutamic acid, erythropoietin injection, dihydroergotoxine, brain protein hydrolysates, murine nerve growth factor, pyritinol, acetylglutamine, piracetam, ethionamide, and hormone replacement therapy (growth hormones, estrogens, thyroid hormones).

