**6.3 Permitted Medications and Treatments**

Symptomatic treatment of other comorbid diseases is allowed, provided it does not affect the evaluation of efficacy and safety. Such treatments must be documented in the eCRF, including generic names or names of therapies, dosage, reasons for use, frequency, and timing, to facilitate analysis and reporting.

Any medications used to treat AEs or for prophylactic purposes during the trial must be meticulously recorded in the eCRF.

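### The drug exclusion looks only at use after injury, so an established user of a Section 6.2 drug with no dose since the injury is eligible and then barred from it for about 104 days

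*Protocol*

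**What the plan says.** Protocol Section 4.2.2 (Exclusion criteria) rules out "Use of prohibited drugs or other cognitive-enhancing drugs listed in the protocol after injury"; the Synopsis carries the same criterion. The time qualifier is the injury. No criterion sets a look-back or washout for use before it.

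Section 6.2 sets a different period: "During the medication and follow-up periods, the use of drugs that might affect the efficacy evaluation is prohibited". Its list includes "Cholinesterase inhibitors such as donepezil, rivastigmine, galantamine, tacrine, and huperzine A" and ends with "hormone replacement therapy (growth hormones, estrogens, thyroid hormones".

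Section 6.3 adds: "Symptomatic treatment of other comorbid diseases is allowed, provided it does not affect the evaluation of efficacy and safety". It makes no separate provision for established replacement therapy.

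Section 1.1.2 gives the protocol's own view of these hormones. It describes estrogens as "significantly influencing the normal functioning of learning, memory, and cognitive processes" and thyroid hormones as regulating gene and protein expression, "thereby affecting brain functions including learning and memory".

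Section 5.8 collects prescription and over-the-counter drugs taken before the trial drug, but attaches no eligibility consequence to the answer.

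**The concern.** The eligibility rule and the concomitant-drug rule cover the same drugs over different periods. A patient who took a listed drug regularly before the accident and missed it afterwards falls between them: nothing in 4.2.2 excludes the patient, and 6.2 forbids the drug from the first day of treatment to the primary assessment.

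Two things are at stake. First, entry depends on whether a home medicine happened to be given in the hours before screening, a distinction with no evident scientific purpose. Second, the protocol asks an eligible patient to remain without an established therapy that it says acts on learning and memory, while it measures cognition as the primary endpoint. The alternative for that patient is a protocol breach.

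**Working it through.** The plan states no figure to reproduce here. The check sets the rules side by side and follows them for each type of patient. The only arithmetic is the length of the ban.

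**Length of the ban.** Inputs: treatment of 14 days with a 1-day window, follow-up of 90 days (Section 5.6), and a Day 90 visit within ± 3 days, counted from the end of medication (Section 5.13).
- Nominal: 14 + 90 = 104 days.
- Shortest: 14 + (90 − 3) = 14 + 87 = 101 days.
- Longest: (14 + 1) + (90 + 3) = 15 + 93 = 108 days.

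**Patient A: established user, given a dose between injury and randomisation.** This is use after injury, so 4.2.2 excludes the patient. The gap does not reach this patient.

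**Patient B: the same history, but no dose since injury.** The drug criterion is not met. Other possible barriers:
- Section 4.1 asks investigators and sponsor to discuss eligibility before enrolment, but sets no rule on prior drugs.
- The investigator-discretion exclusion in 4.2.2 permits exclusion but does not require it, so the 74 centers named in Section 3.1 may decide differently.
- No criterion names pre-existing dementia. Neurological disorders exclude only where they stand in the way of cooperation, and the MMSE inclusion cut-offs can also be met by someone impaired before the injury.

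Patient B is therefore eligible under the written rules. The drug is already interrupted at baseline. Two paths follow.

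- **B1, stays off the drug.** The interruption runs for a further 101 to 108 days, through the Day 90 LOTCA. The documents do not say how quickly the effect of a listed drug fades, so whether it has gone by the baseline LOTCA or fades between baseline and Day 90 is unknown. In the second case it enters the change score.
- **B2, resumes the drug.** This breaches 6.2. Section 4.3.1 counts use of treatment drugs outside the protocol as poor compliance and a ground for withdrawal decided by the investigator. It also lists meeting an exclusion criterion, and resuming a listed drug is, read literally, use after injury. If the patient leaves during follow-up, Section 13 carries the last observation forward. The Trial Schedule places LOTCA at screening, end of treatment and Day 90, so an end-of-treatment score, nominally 90 days early, would stand in for the primary value. A breach judged serious at data review would also remove the patient from the per-protocol set.

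**Size.** The number of B patients is the number enrolled who used a listed drug before injury and had no dose between injury and randomisation. The protocol gives neither quantity, nor the effect of interruption on LOTCA. The effect on power cannot be computed from it.

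**The case against.** The strongest case on the other side is that this is a narrow gap with partial safeguards. Much of that stands.

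- **Scope.** A reader might infer that all pre-injury users are admitted and then stop their drug. The documents do not support this. Anyone with a dose after injury is excluded, and those who do enter are already off the drug at baseline, so they are kept off it.
- **Bias.** A reader might infer that the treatment comparison is biased. Allocation is by centralised block randomisation (Section 12), so such patients are balanced across arms on average. Interruption of a background drug adds noise to LOTCA change; it does not systematically shift the between-arm difference.
- **Loss of patients.** Withdrawal under 4.3.1 is an investigator's decision. Section 4.3.3 asks for a last assessment as far as possible, and Section 13 keeps every dosed patient in the full analysis set. A breach does not automatically lose the primary value.
- **6.2 against 6.3.** A reader might see a contradiction. The proviso in 6.3 can be read as deferring to the 6.2 list, so the two are consistent. What remains is that established replacement therapy is not addressed.
- **Power.** A reader might assume a share of users and a nil treatment effect among them and derive a loss of power. Neither figure is in the protocol, and a share covering all users would overstate the group, which is limited to those with no dose since injury.

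The safeguards do not close the gap. Discussion before enrolment, investigator discretion and a recorded medication history make such patients identifiable, but none says what to do with them.

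**Conclusion.** The point holds in this limited form. Followed exactly, the written rules make eligibility depend on whether a home dose was given before screening, and they admit some patients whose established therapy Section 6.2 then forbids. The consequences are added variability in LOTCA change, possible per-protocol exclusions or carried-forward primary values, and an unanswered participant-safety question about interrupted replacement therapy.

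The conclusion rests on the plain reading of the time qualifiers in 4.2.2 and 6.2, and on Section 1.1.2 for the view that the listed hormones act on cognition. It needs no assumption about prevalence. It does not threaten the validity of the primary comparison, but it should be corrected because the wording can be repaired cheaply.

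**What to change.** Reconcile Section 4.2.2, the Synopsis, Section 6.2 and Section 6.3 so that:

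1. eligibility states explicitly how regular use of a 6.2 drug before the injury is treated, applied from the medication history already collected under Section 5.8; and
2. no patient is eligible whose established replacement therapy 6.2 then forbids.

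Which of these sections changes, the clinical rule itself and any look-back period are for the sponsor to set.

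The cost is an amendment to the wording of those sections and possibly a few more screen failures. No procedure or visit is added.
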